## Abstract

**Background:**

Chronic daily headaches (CDH) are common and associated with significant morbidity, poor quality of life, and substantial burden on the healthcare system. CDH tends to be refractory to conventional medical management and/or patients cannot afford expensive treatments. It is stipulated that CDH share a mechanism of central sensitization in the trigeminocervical complex, mediated by activation of the *N*-methyl-d-aspartate (NMDA) receptors. Ketamine, a non-competitive NMDA antagonist, has been used in the treatment of chronic pain, but its role in CDH has not been completely established. This trial aims to evaluate the effect of high-dose IV ketamine infusions (compared to placebo) on the number of headache days at 28 days post-infusion.

**Methods:**

A multicenter, placebo-controlled, randomized controlled trial will be conducted with two parallel groups and blinding of participants and outcome assessors. The study will include 56 adults with a CDH diagnosis as per ICHD-3 criteria. Participants will be randomized (1:1) to either ketamine (1 mg. kg^−1^ bolus followed by infusion of 1 mg. kg^−1^. h^−1^ for 6 h) or placebo (0.9% saline in the same volume and infusion rate as the trial medication) bolus and infusion for 6 h. The impact on the number of monthly headache days, headache intensity, physical activity, mood, sleep, quality of life, analgesic consumption, and adverse effects will be recorded at baseline, immediately post-infusion, and from 1 to 28 days, 29 to 56 days, and 57 to 84 days after the infusion

**Discussion:**

Despite advancements in treatment, many patients continue to suffer from CDH. This trial investigates whether high-dose IV ketamine infusions can effectively and safely improve the CDH burden as compared to a placebo infusion. This treatment could become a safe, affordable, and widely available option for patients living with refractory headache.

**Trial registration:**

ClinicalTrials.gov NCT05306899. Registered on April 1, 2022

**Supplementary Information:**

The online version contains supplementary material available at 10.1186/s13063-023-07186-3.

## Administrative information

World Health Organization Registration Data Set

## Introduction

### Background and rationale

The prevalence of primary chronic daily headaches (CDH) is 5% in the population and is associated with significant morbidity, a poor quality of life, and a substantial burden on the healthcare system [1]. Important subtypes of CDH include chronic migraine, chronic tension-type headache, hemicrania continua, new daily persistent headache, and medication overuse headache [2–5]. Many patients with CDH do not respond to conventional medical management that includes medications, nerve blocks, and psychological approaches, and adverse events with these treatments are also common [6, 7]. Although onabotulinum-toxin A and calcitonin gene-related peptide (CGRP) antagonists are promising new treatments for CDH, these are expensive and their long-term effects are unclear. There is an urgent need for efficacious, safe, inexpensive, and widely available treatments for patients with CDH.

The subtypes of CDH share central sensitization, an increase in neuronal excitability secondary to repetitive stimulation of the nociceptive C-fibers (“wind-up”) in the trigeminocervical complex (TCC) and the brain, as a common mechanism [8–10]. The TCC contains major relay neurons for nociceptive afferent input from the meninges and cervical structures and its sensitization is a key feature of CDH. Central sensitization is mediated primarily by *N*-methyl-d-aspartate (NMDA) receptors. Activation of the NMDA receptors also plays a major role in ongoing pain, opioid-induced hyperalgesia, and mood dysregulation [10]. This sensitization can be reversed on a long-term basis by the blockade of NMDA receptors by non-competitive antagonists such as ketamine [8–10]. Intravenous (IV) ketamine in high doses (0.4 to 1 mg. kg^−1^ .h^−1^) has been used to treat NMDA receptor-driven neuropathic pain syndromes [8].

Recently, ketamine administered through IV and other routes has been investigated for its role in refractory headaches in observational studies [11–13] and a few small randomized controlled trials (RCT) [14–16]. This evidence suggests analgesic benefit, but it is of low quality, and there is considerable heterogeneity across the studies in terms of indications, dose, and route of administration of ketamine and the pain-associated domains that have been assessed [17]. Recent evidence also shows that infusions of ketamine 1 mg kg^−1^ h^−1^ are associated with greater and sustained pain relief as compared to only a bolus and or low-dose infusion regimens [8, 10, 17].

#### Rationale

CDH poses a significant burden on patients, healthcare systems, and society. IV ketamine infusion, an intervention that is widely available and scalable, can treat CDH by reversing the NMDA receptor-mediated sensitization of the TCC. This KetHead trial is the first multicenter, placebo-controlled, parallel-group randomized trial with blinding of participants and observers and with the goal of comprehensively assessing the effect of high-dose IV ketamine infusion (1 mg. kg^−1^. h^−1^ for 6 h) on the frequency and intensity of headaches, mood, activity, sleep, quality of life, and safety of ketamine for 84 days after the interventions, as compared to placebo.

### Objectives

The following is the primary objective:To determine the number of days with headache in the first 28 days after the ketamine infusion

The following are the secondary objectives:To determine the number of days with headache from 29 to 56 days and 57 to 84 days after the infusionTo determine the average intensity and duration of headaches headache from 1 to 28 days, 29 to 56 days, and 57 to 84 days after the infusionTo determine the number of days until recurrence of headache after infusionTo determine the daily requirement for analgesics at 28, 56, and 84 days after the infusionTo determine the quality and duration of sleep at 28, 56, and 84 days after the infusionTo determine the average daily physical activity and interference in functioning from CDH at 28, 56, and 84 days after the infusionTo assess mental health domains (depression, anxiety, and pain catastrophizing) at 28, 56, and 84 days after the infusionTo assess the quality of life and participants’ impression of change at 28, 56, and 84 days after the infusionTo assess the prevalence of adverse effects at 7, 28, 56, and 84 days after the infusion

### Hypothesis

The primary hypothesis of this trial is that patients with CDH undergoing high-dose ketamine infusion will report a decrease in the number of headache days in the first 28 days after the infusion as compared to the saline infusion (placebo).

The secondary hypotheses of this trial are that patients with CDH undergoing high-dose ketamine infusion will report a decrease in the number of headache days and daily requirement of analgesics and show an improvement in quality and duration of sleep, physical activity, mental health, and quality of life as compared to the saline infusion (placebo).

### Trial design

The KetHead trial is designed as a multi-center, placebo-controlled, superiority randomized controlled trial with two parallel groups and blinding of participants and outcome assessors. Randomization will take place upon participant enrollment. Randomization will be to one of two arms, with a 1:1 allocation and permuted blocks of six. The randomization sequence will be computer-generated, and allocation concealment will be ensured by sequentially numbered, sealed opaque envelopes. This process will be carried out by an independent research coordinator, who is not involved in the recruitment process or conduct of the trial. An unblinded pharmacist will dispense the trial medication to an unblinded and delegated healthcare provider who will then prepare the trial medication according to protocol and then present it to a blinded physician, who will administer the trial medication according to the protocol. A blinded member of the research team will perform an outcome assessment. Treating physicians, participants, close contacts, trial coordinators, and primary outcome assessors will be blinded to treatment allocation.

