### Eligibility criteria

The inclusion and exclusion criteria are listed in Table 1. After enrollment, bloodwork to rule out hepatic and/or renal impairment is ordered if no recent (within 12 months) information is available. Additionally, on the day of the intervention, a pregnancy test is performed for each female participant less than 50 years of age.

**Table 1 Tab1:** Inclusion and exclusion criteria

***Inclusion criteria*****:** 1. Age 18 years or older 2. CDH diagnosis according to the International Classification of Headache Disorder – 3rd edition [18] 3. Normal liver and kidney function ***Exclusion criteria*****:** 1. Pregnant or breastfeeding participants 2. Pre-existing renal impairment: stage 4 chronic kidney disease 3. Pre-existing liver impairment, defined as alanine transaminase (ALT) and/or aspartate aminotransferase (AST) greater than two times the upper normal limit, an elevated total bilirubin (TB), an elevated alkaline phosphatase (AP), an elevated international normalized ratio (INR) for prothrombin time, and/or an elevated blood urea nitrogen (BUN) 4. Chronic benzodiazepine or antipsychotic medication use 5. History of a cerebrovascular event 6. Significant and untreated hypertension and severe cardiac decompensation 7. Pheochromocytoma 8. Hyperthyroidism 9. Glaucoma 10. Concomitant use of strong CYP2B6 or CYP2C8 inhibitor 11. Allergy or intolerance to ketamine 12. Any significant cognitive or language barriers that impede participation 13. Use of calcitonin gene-related peptide antagonists in one month or onabotulinum-toxin A in 3 months prior to the trial medication infusion, that is associated with greater than 30% reduction in headache intensity or number of migraine days 14. Active diagnosis of post-traumatic stress disorder 15. Active diagnosis of substance use disorder 16. Daily oral morphine equivalent (OME) of 80 mg or higher	

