##### Control group

For individuals randomized to the saline infusion group, an IV bolus of 0.9% saline (0.1 ml. kg^−1^) will be given. This is followed by an infusion of 0.5 mL. kg^−1^. h^−1^ of saline for 6 h. The volume of bolus and rate of the infusion will be the same as that of a ketamine infusion for the body weight to prevent unblinding of participants and assessors.

We will use an approved Health Canada-marketed version of ketamine hydrochloride for this trial. The trial medication will be prepared by appropriately qualified health personnel in order to ensure the integrity of the trial protocol and to maintain blinding. The pharmacist dispensing the trial medication will not be blinded but they will not interact with the trial participants at any stage. When a patient is randomized, the delegated clinical nurse will check the corresponding treatment number (as assigned through an opaque sequentially numbered allocation envelope) and provide a prescription to the pharmacist to dispense the trial medication. In the event a subject is randomized but never administered any trial medication, the treatment will not be reassigned. Trial medication preparations are subject-specific only and will not be administered to another patient.

Trial personnel will assess the patient and collect data throughout their enrollment in the trial.

During the trial, participants will be instructed to use a pain and migraine diary for the collection of data on migraine days, pain scores, and rescue pain medication during the first 84 days after the infusion.

Participants will be assessed for the collection of outcomes immediately after the infusion and during the first 84 days after the infusion.

Participants in both arms will wear an actigraphy device (Additional file 1: Appendix 1) to assess the quality and duration of sleep and activity for 1 week prior to the trial medication infusion (for collection of baseline data) and starting on the day of infusion for 1 month after the infusion to longitudinally assess the impact of the trial treatments on sleep and activity.

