**Fig. 2 Fig2:**
[figure not shown]
Schedule of enrollment, interventions, and assessments. -*t*1, 28 days before infusion; 0: day of infusion; *t*1, end of infusion; *t*2, at 7 days post-infusion; *t*3, at 28 days post-infusion; *t*4, at 56 days post-infusion; *t*5, at 84 days post-infusion

The screening for eligibility to participate in this trial and the informed consent occurs within 3 to 6 months before the intervention (Additional file 2: Appendix 2). The trial starts a month prior to the day of the infusion, as the patient will start tracking the number of headache days and the daily pain score 28 days prior to the infusion date. This baseline headache diary will be collected on the day of the infusion. On that same day, the participant will fill out the validated questionnaires (completing baseline assessment). Baseline data on sleep and physical activity will also be collected using actigraphy over 1 week prior to the trial infusion. Scheduled follow-up visits at 28, 56, and 84 days after the trial infusion will be performed in-person or virtually (video/phone) to assess trial-relevant outcomes.

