### Sample size

A difference of 3 headache days (standard deviation (SD) of 3.8) in the frequency of headache days between the two groups in the 28 days after the trial infusion is considered as a minimum clinically important difference (MCID) [32] for this trial. A sample size of 25 participants in each group would have over 80% power to detect this difference between the 2 groups using a two-sided alpha of 0.05. Assuming a 10% drop-out rate 1 month after the infusions, 28 participants will be enrolled in each arm. This sample size is also robust to capture a key secondary outcome for this trial—a MCID of 1.0 (SD 1.3) in the mean 0–10 NRS score for average intensity of headaches in the first 28 days after the infusions (power of over 80% with a two-sided alpha 0.05) [14].

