## Assignment of interventions

### Randomization, sequence generation, and allocation concealment

Upon participant enrollment, patients will be randomized to one of two arms, with a 1:1 allocation and random permuted blocks of six. The randomization sequence will be computer generated by a member of the research team. The treatment allocation will be performed by an independent research coordinator not otherwise involved in the study, who will ensure allocation concealment by sequentially numbered, sealed opaque envelopes. This allocation sequence will be provided to the unblinded pharmacist

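### Randomisation is fixed at enrolment, before the last eligibility checks and the baseline diary, so people who are never infused can be randomised without a definable primary outcome and without a sample-size allowance

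*Protocol article*

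**What the plan says.** Two sections fix the time of randomisation. Trial design says "Randomization will take place upon participant enrollment", and the section on randomization and sequence generation repeats it: "Upon participant enrollment, patients will be randomized to one of two arms, with a 1:1 allocation and random permuted blocks of six".

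Other sections place later steps relative to enrolment or to the infusion:

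- Participant timeline: "The screening for eligibility to participate in this trial and the informed consent occurs within 3 to 6 months before the intervention". On the baseline diary it says that "the patient will start tracking the number of headache days and the daily pain score 28 days prior to the infusion date", and that the diary is handed in on the infusion day.
- Eligibility criteria: "After enrollment, bloodwork to rule out hepatic and/or renal impairment is ordered if no recent (within 12 months) information is available". It adds that "on the day of the intervention, a pregnancy test is performed for each female participant less than 50 years of age".
- Table 1, exclusion 13: the look-back is counted from the infusion, 1 month for CGRP antagonists and 3 months for onabotulinum-toxin A.
- Control group: "In the event a subject is randomized but never administered any trial medication, the treatment will not be reassigned". The same section has the nurse check the treatment number and send the prescription when a patient is randomised.
- Primary clinical outcome: headache days are counted over the 28 days that follow the infusion.
- Statistical methods: analysis is by intention to treat, and missing primary values are not imputed. One sensitivity analysis treats those lost to follow-up as unchanged in headache frequency. ANCOVA adjusts for the 28-day baseline.
- Sample size: "Assuming a 10% drop-out rate 1 month after the infusions, 28 participants will be enrolled in each arm".

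**The concern.** Followed as written, this order lets a person be randomised and then fail an eligibility check, or withdraw, before any infusion. Two things follow.

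First, the primary outcome window starts at the infusion, so a never-infused participant has no day 1. The protocol foresees such people but says only that their treatment is not passed on. An intention-to-treat analysis without imputation then has no value for them. The no-change sensitivity analysis does not clearly help: it needs a baseline count, and anyone who leaves before finishing the diary has none.

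Second, the 10% allowance is counted one month after the infusions. Losses between randomisation and infusion are not budgeted, and the design has no slack to absorb them.

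**Working it through.** **Order of events under two readings of enrolment**

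The text gives enrolment no date of its own. Feasibility of recruitment supports reading it as consent: 37 consenting in 12 months is projected to 56 enrolled in 18 months, and 37 × 18/12 = 55.5, so every consenting person is counted as enrolled. On the other side, Participant timeline says that the trial starts a month before the infusion, and the Fig. 2 legend lists no time point earlier than 28 days before it.

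| Step | Enrolment = consent (3 to 6 months before) | Enrolment = diary start (about 28 days before) |
|---|---|---|
| Bloodwork, if no result in 12 months | after randomisation | after randomisation |
| Exclusion 13 windows (1 and 3 months) | wholly or almost wholly after | partly after |
| Baseline diary completed | after | after |
| Pregnancy test | after | after |

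The length of the gap changes between the readings. The order does not.

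**The plan's own sample size**

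Inputs from Sample size: difference 3 days, SD 3.8, two-sided alpha 0.05, 25 per group, 10% drop-out.

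- Non-centrality = 3 / (3.8 × √(2/25)) = 2.79.
- Normal approximation: Φ(2.79 − 1.96) = 79.7%. Non-central t with 48 degrees of freedom: 78.1%.
- 25 / 0.9 = 27.8, rounded up to 28 per arm.

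The plan's figures are reproduced closely, although the claim of over 80% is slightly optimistic. With 28 enrolled, 28 × 0.9 = 25.2 remain, so the allowance is fully used by post-infusion loss.

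**Adding loss before the infusion**

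The protocol gives no rate for this, so q below is an assumption. Evaluable per arm = 28 × (1 − q) × 0.9, with no replacement. The number to randomise per arm to keep 25 evaluable = 25 / ((1 − q) × 0.9), rounded up.

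| q (assumed) | Evaluable per arm | Power, t-test | Power, normal | Randomised per arm to keep 25 |
|---|---|---|---|---|
| 0% | 25.2 | 78.4% | 80.0% | 28 |
| 5% | 23.9 | 76.2% | 78.0% | 30 |
| 10% | 22.7 | 73.9% | 75.8% | 31 |
| 20% | 20.2 | 68.6% | 70.8% | 35 |

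By the t-test, the cost is 78.4 − 73.9 = 4.5 points at 10% loss and 78.4 − 68.6 = 9.8 points at 20%.

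**The case against.** The strongest reply is that the protocol never says that randomisation happens months ahead. What it dates at 3 to 6 months is screening and consent. Having the nurse act on the treatment number and send the prescription when a patient is randomised suggests a moment near dispensing, and the figures that might settle this are not shown. This stands: a gap of months is one reading only. It does not remove the point, because two sections tie randomisation to enrolment, and the bloodwork sentence places an eligibility check after enrolment on any reading.

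A reader might also infer more than the text supports:

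- *All eligibility bloodwork follows randomisation.* It does so only for those with no result in the past 12 months.
- *A never-infused participant cannot be replaced.* The sentence on reassignment concerns the allocation and its preparation and is silent on further enrolment. The power losses above therefore hold only without replacement.
- *Early allocation lets unblinded staff influence the baseline diary.* No mechanism is described. Blinded participants keep the diary, the pharmacist does not meet them, and the pharmacist is given the sequence in any case.
- *Intention to treat must be broken and the result biased.* Under the blinding described, pre-infusion loss should be similar in both arms. How never-dosed participants enter the analysis set may also be settled in a document not shown.

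Finally, the power figures ignore the planned baseline adjustment. ANCOVA power depends on a baseline correlation that the protocol does not give.

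**Conclusion.** The point holds in this form: the stated time of randomisation precedes checks that can still exclude a participant and precedes the completed baseline covariate, and neither the outcome definition nor the drop-out allowance covers those lost in between. The sections on trial design, randomisation, control group and participant timeline also need reconciling on when randomisation occurs.

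The size is moderate and conditional. An assumed 5% to 20% pre-infusion loss without replacement takes t-test power from about 78% to between about 76% and 69%, unadjusted for baseline. The consequence is lost power and an incomplete intention-to-treat set. The document does not demonstrate bias.

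**What to change.** State that the allocation envelope is opened on the infusion day, after the baseline diary has been collected and the bloodwork, pregnancy test and all eligibility criteria are confirmed. Count the 56 as randomised at that point, and align the four sections. The present 10% allowance then covers the loss it was meant for.

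Consent and screening stay as they are. The costs are same-day dispensing and preparation, and somewhat more consenting people to reach 56. At an assumed 10% pre-infusion loss, 56 / 0.9 = 62.2, so 63 consents; at 37 a year that is 63 / 37 × 12 = 20.4 months, against 56 / 37 × 12 = 18.2.

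If the timing cannot change, define the outcome window and analysis set for the never-infused, say whether they are replaced and, if they are not, raise the number randomised (31 per arm at an assumed 10% loss). Recruitment began in August 2022, so those definitions are also needed, before unblinding, for anyone already randomised under the present wording.

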## Methods

### Trial setting

The trial will be conducted at two sites: Toronto Western Hospital (University Health Network) and Sinai Health System, both in Toronto, Ontario, Canada.

### Eligibility criteria

The inclusion and exclusion criteria are listed in Table 1. After enrollment, bloodwork to rule out hepatic and/or renal impairment is ordered if no recent (within 12 months) information is available. Additionally, on the day of the intervention, a pregnancy test is performed for each female participant less than 50 years of age.

**Table 1 Tab1:** Inclusion and exclusion criteria

***Inclusion criteria*****:** 1. Age 18 years or older 2. CDH diagnosis according to the International Classification of Headache Disorder – 3rd edition [18] 3. Normal liver and kidney function ***Exclusion criteria*****:** 1. Pregnant or breastfeeding participants 2. Pre-existing renal impairment: stage 4 chronic kidney disease 3. Pre-existing liver impairment, defined as alanine transaminase (ALT) and/or aspartate aminotransferase (AST) greater than two times the upper normal limit, an elevated total bilirubin (TB), an elevated alkaline phosphatase (AP), an elevated international normalized ratio (INR) for prothrombin time, and/or an elevated blood urea nitrogen (BUN) 4. Chronic benzodiazepine or antipsychotic medication use 5. History of a cerebrovascular event 6. Significant and untreated hypertension and severe cardiac decompensation 7. Pheochromocytoma 8. Hyperthyroidism 9. Glaucoma 10. Concomitant use of strong CYP2B6 or CYP2C8 inhibitor 11. Allergy or intolerance to ketamine 12. Any significant cognitive or language barriers that impede participation 13. Use of calcitonin gene-related peptide antagonists in one month or onabotulinum-toxin A in 3 months prior to the trial medication infusion, that is associated with greater than 30% reduction in headache intensity or number of migraine days 14. Active diagnosis of post-traumatic stress disorder 15. Active diagnosis of substance use disorder 16. Daily oral morphine equivalent (OME) of 80 mg or higher	

